**Premedication**

Premedication for subsequent taliglucerase alfa infusions may be considered at the discretion of the investigator and Medical Director for subjects experiencing early clinical signs of hypersensitivity or rash/urticaria that responds promptly to oral antihistamine administration (see also Appendix 2 for adjustment of infusion rate). The premedication will be applied according to the following steps as needed to prevent progressive hypersensitivity:

1. Antihistamine (H1 blocker: diphenhydramine, hydroxyzine, cetirizine, loratadine, desloratidine) at a standard dose 12 hours and 2 hours before the start of the infusion.
2. H1 blocker plus H2 blocker (ranitidine, cimetidine, famotidine) at standard doses 12 hours and 2 hours before the start of the infusion.
3. H1 blocker plus H2 blocker plus prednisone up to 50 mg administered 12 hours and 2 hours before the start of the infusion.

## **13.4 Appendix 4. MRI**

### **13.4.1 Subjects and sites**

Approximately 10 subjects will be enrolled in this trial by 5 to 10 sites world wide.

### **13.4.2 Magnetic Resonance Imaging (MRI) data**

Each subject enrolled in this trial will have 2 MRI timepoints during the course of the trial at Baseline and Month 12.

For each timepoint, the same set of T1 and T2-weighted MRI sequences will be acquired. These sequences will be defined based on their equipment and abilities to provide sufficient image quality and contrast for organ (spleen and liver) detection and quantification, and also full spleen and liver coverage in Gaucher subjects. No contrast agent will be used. If baseline MRI cannot be obtained, organ volumes can be obtained by ultrasound technology with approval of the Medical Director.

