## **5 STUDY OBJECTIVES**

The efficacy objectives of this trial are to assess the efficacy of taliglucerase alfa in subjects between 2 to < 18 years old with Gaucher disease, as measured by percent change in haemoglobin, chitotriosidase or CCL18, spleen and liver volume evaluated by MRI (or ultrasound), and platelet count, and change in growth and development (height, weight, Tanner Stage, bone age), bone disease, and Quality of Life from baseline.

The safety objectives are to assess the safety of taliglucerase alfa by clinical laboratory, physical examination, echocardiography, adverse events and anti-taliglucerase alfa antibodies

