## **8 EFFICACY AND SAFETY ASSESSMENTS**

### **8.1 Efficacy Variable(s)**

- The primary efficacy variable is median percentage and the interquartile range for change from baseline in haemoglobin
- Secondary efficacy variables are:
  - Percent change from baseline in chitotriosidase or CCL18
  - Percent change from baseline in spleen and liver volume (see Appendix 4)
  - Percent change from baseline in platelet count
- Exploratory endpoints are:
  - Change in height and weight
  - Change in Tanner Stage
  - Change in bone age by X-ray of left hand and wrist
  - Change in bone density by DEXA
  - Occurrence of bone crises
  - Quality of Life using the Child Health Questionnaire™ (CHQ) PF-28 (valid for subjects aged 5 to 18 years)

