| TSH, transferrin, B12 and folic acid    | X                    |                     |                                                     |                    |                                 |                     |                             |                     |                                 |          |
| Beta HCG (post-menarchal girls)         | X                    |                     |                                                     |                    |                                 |                     |                             |                     |                                 |          |
| Urinalysis                              | X                    | X                   | X                                                   | X                  |                                 | X                   |                             | X                   |                                 | X        |
| Review inclusion/exclusion criteria     | X                    |                     |                                                     |                    |                                 |                     |                             |                     |                                 |          |
| Anti-taliglucerase alfa antibodies      |                      | X                   |                                                     | X                  |                                 | X                   |                             | X                   |                                 | X        |
| Organ volumes (MRI/ultrasound)          |                      | X                   |                                                     |                    |                                 |                     |                             |                     |                                 | X        |
| Tanner Stage                            |                      | X                   |                                                     |                    |                                 | X                   |                             |                     |                                 | X        |

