### **9.2.2 Visit 1 (Baseline, Day 1)**

1. Assign to randomized treatment group
2. Concomitant medications
3. Physical examination including weight and height
4. MRI or ultrasound for spleen and liver volume
5. Echocardiography (for tricuspid insufficiency gradient)
6. Clinical laboratory tests
  - Blood platelet count and hemoglobin (local)
  - Haematology
  - Biochemistry
  - Urinalysis
  - Anti-taliglucerase alfa antibody
  - Biomarkers: chitotriosidase or CCL18
  - Mutation analysis
7. Left hand and wrist X ray for bone age
8. Tanner Stage

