#### **9.2.10 Visit 28 (Month 12, Week 52 $\pm$ 7 days)**

Perform the following assessments:

1. Adverse events and concomitant medications
2. Physical examination including weight and height.
3. Clinical laboratory tests
  - Blood platelet count and hemoglobin (local lab)
  - Haematology
  - Biochemistry
  - Urinalysis
  - Anti-taliglucerase alfa antibodies
  - Biomarkers: Chitotriosidase or CCL18
4. Quality of life
5. Echocardiography
6. Spleen and liver volume by MRI or ultrasound
7. Tanner Staging
8. Left hand and wrist X-ray for bone age

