**13.4.5.2 Centralized Image Review by Independent Readers**

The MRI data will be centrally evaluated in a fully blinded manner by an independent reader. The reading sessions will be organized at the imaging CRO site. The same image evaluation procedure will be used for all subjects' MRI scans in this trial.

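### Spleen and liver volume may be measured by MRI or ultrasound, and nothing requires the same method at baseline and Month 12 within a child

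*Protocol*

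**What the plan says.** Protocol section 8.1 makes percent change from baseline in spleen and liver volume a secondary efficacy variable and refers to Appendix 4. The method is described in several places, and they do not agree.

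- Section 9.2.2 (Visit 1, baseline) lists "MRI or ultrasound for spleen and liver volume".
- Section 9.2.10 (Visit 28, Month 12) lists "Spleen and liver volume by MRI or ultrasound".
- The objectives (section 5) and the flow chart (section 9.1) likewise name both methods and attach no condition.
- Appendix 4, section 13.4.2, starts from MRI: "Each subject enrolled in this trial will have 2 MRI timepoints during the course of the trial at Baseline and Month 12". It then gives the exception: "If baseline MRI cannot be obtained, organ volumes can be obtained by ultrasound technology with approval of the Medical Director".

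The only sameness requirement, also in 13.4.2, concerns the MRI sequences used at each time point. On reading, section 13.4.5.2 says "The MRI data will be centrally evaluated in a fully blinded manner by an independent reader". The reader is also kept blind to the order of the time points by randomised display of the MRI scans. No equivalent procedure is described for ultrasound.

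**The concern.** A percent change within a child is interpretable when both volumes come from the same method, because a constant proportional difference between methods then cancels. If the methods differ between visits, that difference goes straight into the result and cannot be separated from the treatment effect.

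The protocol foresees that some baseline MRIs will fail, so the situation is not hypothetical. The visit lists leave the Month 12 method open, and the appendix addresses only failure at baseline. A site can therefore follow the protocol and still produce a mixed pair. With 10 planned subjects and no replacement of withdrawals (section 6.3.4), each pair carries weight.

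**Working it through.** **Text check.** The places that govern the method, side by side:

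| Place | Ultrasound allowed when | Tied to the baseline method? |
|---|---|---|
| 9.2.2, Visit 1 | No condition stated | Not applicable |
| 9.2.10, Visit 28 | No condition stated | No |
| 9.1, flow chart | No condition stated | No |
| 13.4.2 | Baseline MRI unobtainable and Medical Director approves | Silent on Month 12 |
| 13.4.8, unevaluable MRI | Not mentioned; documentation and corrective action only | No |

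Two conclusions follow. The visit lists and the appendix state different conditions for ultrasound. And no place requires one method per subject.

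**Size (illustration).** The protocol states no figure on this point that could be reproduced, and no ultrasound-MRI agreement figure. The method difference is therefore an assumption.

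Inputs:
- True change *t*: liver -10.48% and spleen -26.91%, both from the 30 units/kg arm of the earlier pivotal study (section 4). They are used only for scale.
- Ultrasound reads (1 + *b*) times the MRI volume, with *b* assumed to be ±5% or ±10%.

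Ultrasound at baseline and MRI at Month 12: observed change = (1 + *t*)/(1 + *b*) - 1.

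| *b* | Liver, true -10.48% | Spleen, true -26.91% |
|---|---|---|
| -10% | 0.8952/0.90 - 1 = -0.53% | 0.7309/0.90 - 1 = -18.79% |
| -5% | 0.8952/0.95 - 1 = -5.77% | 0.7309/0.95 - 1 = -23.06% |
| 0 | -10.48% | -26.91% |
| +5% | 0.8952/1.05 - 1 = -14.74% | 0.7309/1.05 - 1 = -30.39% |
| +10% | 0.8952/1.10 - 1 = -18.62% | 0.7309/1.10 - 1 = -33.55% |

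The liver change would vanish at 1 + *b* = 0.8952, that is, if ultrasound read about 10.5% below MRI.

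Same method at both visits: (1 + *t*)(1 + *b*)/(1 + *b*) - 1 = *t*, so a constant proportional difference drops out.

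**Weight of one child.** With 10 subjects and an assumed 1:1 allocation (section 7.7 gives no ratio), an arm has 5 children and one mixed pair is 1/5 = 20% of it. The arm's mean liver change moves by (observed - true)/5:
- *b* = -10%: (-0.53 + 10.48)/5 = +1.99 points
- *b* = -5%: (-5.77 + 10.48)/5 = +0.94 points
- *b* = +5%: (-14.74 + 10.48)/5 = -0.85 points
- *b* = +10%: (-18.62 + 10.48)/5 = -1.63 points

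These shifts compare with a true mean of about -10.5%. A median would respond differently, depending on where the affected child falls.

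**The case against.** The best defence is that Appendix 4 governs. Section 8.1 points to it, the visit lists are one-line reminders, and the exception speaks of organ volumes in general after a failed baseline MRI. That can be read as moving the child's whole series to ultrasound, and listing ultrasound at Visit 28 fits this. The reading is fair. It means that a reader who infers that a child with a baseline ultrasound must have MRI at Month 12 goes too far. The sentence on two MRI time points suggests that, but a child whose baseline MRI failed is already outside it. What stands is that the text settles neither reading. Nor does Appendix 4 offer ultrasound when only the Month 12 MRI fails; that reverse pair rests on the Visit 28 wording alone.

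Three further inferences are tempting and unsupported:

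- **Ultrasound would be read locally by someone who knows the visit.** No section says who reads it, and section 13.4.4 centralises image management in general terms. The documents show only that no ultrasound reading procedure is described.
- **Ultrasound would fall mainly on the youngest children, so the error would follow age.** Section 13.4.4.2 offers sedation as a way to obtain MRI and does not link ultrasound to age.
- **The method difference is as large as the liver effect.** That needs the top of an assumed range. At 5% a liver reduction still shows.

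It can also be said that handling of mixed pairs belongs in the SAP, which is not at hand, and that section 10 has no text in this copy. That is right for the analysis rule. It does not answer the acquisition gap: an SAP can drop or flag a mixed pair but cannot make the Month 12 scan match baseline.

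**Conclusion.** The point holds as a gap in the measurement rule together with a conflict between the visit lists and Appendix 4. The protocol as written permits, but does not require, a percent change in organ volume that mixes ultrasound and MRI, and it describes blinded reading for MRI only.

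The size is unknown from the document. Under an assumed 5% difference, with ultrasound first, a liver change of -10.5% reads -5.8% or -14.7%. Under 10% it reads -0.5% or -18.6%. Spleen is affected less in relation to its larger effect. One mixed child would move a five-child arm's mean liver change by about 1 to 2 points. These figures rest on the assumed method difference, on effects borrowed from the pivotal study's 30 units/kg arm rather than from a 12-month paediatric result, and on 1:1 allocation.

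The endpoint is secondary (haemoglobin is primary), and Appendix 4 treats ultrasound as an exception. The protocol should be corrected on this point, but the primary analysis is not affected.

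**What to change.** Reconcile sections 9.2.2, 9.2.10 and 13.4.2, with the flow chart to match:

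1. At baseline, MRI is the method; ultrasound is used only if MRI cannot be obtained and the Medical Director approves.
2. At Month 12, each subject is measured by the method used at baseline. A subject with a baseline ultrasound has ultrasound at Month 12, even if MRI is also done. An MRI-first rule should not be repeated at Month 12, because after a baseline ultrasound it would create the mixed pair.
3. Say how ultrasound volumes are read, including whether the reader is blind to treatment and time point.
4. If a mixed pair still occurs, leave it out of the percent-change summary and list it separately. This sentence may sit in the protocol or the SAP.

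The cost is mainly protocol wording, plus a short reading procedure for ultrasound. The small downside is that any mixed pair is lost to this secondary endpoint.

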### **13.4.3 MRI evaluation parameters**

The following MRI parameters will be evaluated during this trial:

- Volume of spleen (in cm^3)
- Volume of liver (in cm^3)

### **13.4.4 Sites and image data management**

All image management activities will be centralized and conducted by an independent imaging Contract Research Organization (imaging CRO) with operational capabilities in Europe and the United States in compliance with all regulatory requirements. An overview of the main activities performed by the imaging CRO is provided in the next sections.

#### **13.4.4.1 Standardization of image acquisition, initial site qualification**

The image acquisition procedure will be standardized by the imaging CRO among all participating sites. The same image acquisition and management procedure will be used by all sites. This procedure will be defined by the imaging CRO and approved by the Sponsor. The sites will be trained and qualified by the imaging CRO prior to start of subject enrolment. Each site will provide test MRI scan(s) during the initial site qualification phase. The source of the test scan(s) will be (in order of preference) a subject volunteer, a healthy volunteer, or the screening image from the first subject tested at the site. All images will be anonymized by the sites (in order to remove any subject-related nominative information) and provided in digital format (DICOM). Only digital images will be centrally processed by the imaging CRO.

---

**13.4.4.2 Subject Sedation**

Pediatric subjects may require sedation in order to obtain the high quality images required. Sites may use standard sedation protocols approved by the institution.

**13.4.4.3 Quality control of image data and site Quality Assurance during the course of the trial**

The image data will be collected and quality controlled by the imaging CRO for checking the technical adequacy, the compliance of data acquisition with the study imaging protocol, the anonymization of the images and the diagnostic quality of the images (their appropriateness for centralized evaluations). If any quality-related issue is detected by the imaging CRO, specific queries will be sent to the sites to implement appropriate corrective (such as potential repeat scans whenever possible) and preventive actions.

**13.4.5 Image processing and centralized analysis****13.4.5.1 Spleen and liver segmentation**

In order to improve the quality of centralized image evaluations, the anatomical structures of interest (liver and spleen) will be pre-detected using automated three-dimensional (3D) segmentation software. 3D segmentation consists in classifying image voxels in multiple tissue classes based on the MRI signal intensities and also the piecewise contiguity of image voxels representing given organs (liver and spleen in this case). The resulting contours representing the liver and the spleen will be manually edited and quality controlled by an expert technician at the imaging CRO. The resulting liver and spleen contours will be submitted for final approval to independent and blinded readers.

**13.4.5.2 Centralized Image Review by Independent Readers**

The MRI data will be centrally evaluated in a fully blinded manner by an independent reader. The reading sessions will be organized at the imaging CRO site. The same image evaluation procedure will be used for all subjects' MRI scans in this trial.

**Expertise of independent readers, training sessions**

The reader will be a Senior Radiologists with a significant experience in liver and spleen imaging and MRI. The reader will provide a detailed, signed and dated CV including scientific references. The imaging CRO will subcontract with the reader for the payment of honoraria.

The reader will be trained prior to start of centralized image review sessions. S/he will be provided with a Reader's Kit including an Image Evaluation Software User Guide. Test cases representing non-study Gaucher subjects (provided by the Sponsor) will be used as well as

potential additional MRI scans from other indications for the training of the readers. Intra- and inter-reader reproducibility rates will be estimated for the quantification of liver and spleen volumes. The potential causes of variability and the main consensus issues (delineation of liver and spleen, specific issues related to Gaucher subjects, technical issues such as partial volume effect, potential movements of organs and image artifacts, etc.) will be discussed with the readers and documented.

### **Conduct of centralized image review sessions**

The reader will be fully blinded with regard to treatment groups, subject's ID and site number. Each MRI timepoint will be evaluated by for the quantification of the liver and spleen volumes. All timepoints will be fully randomized and displayed separately. All evaluations will be performed after collection of Baseline and month 12 timepoint of a pre-defined number of subjects before starting the review sessions. In order to leave the reader blinded with respect to the time sequence, the reader will not be aware of the order of the MRI timepoints which will be fully randomized by the imaging CRO.

All evaluation results including spleen and liver contours, and the imaging CRO electronic Case Report Forms (eCRFs) will be saved in the trial database. In compliance with regulatory requirements (including FDA's 21 CFR Part 11), audit trails will be generated for all image manipulation and evaluation steps and the readers will use an electronic signature system to authenticate themselves for the evaluation of each MRI timepoint. The trial specific Image Review Software will be developed, validated and documented by the imaging CRO in compliance with regulatory requirements.

#### **13.4.6 Data and report transfers to Sponsor**

- Review sessions will be exported to the Sponsor using a pre-defined, standardized and secure data transfer procedure.
- Subject and MRI data tracking information (study progress reports) will be communicated to the Sponsor using a pre-defined, standardized and secure data transfer procedure.
- The final Study database will be submitted to the Sponsor in digital format.
- Spleen and liver volumes will be directly computed from organ masks validated by the blinded reader. The result of this quantification will be stored in the database. The file containing final results will be automatically generated from the values of the database, thus avoiding any result to be modified after the review sessions.

#### **13.4.7 Direct access to Study data**

- A Direct access to Study data will be made possible by the imaging CRO for audit purposes.
- Such Study data include:

- 
- Information related to interactions between the imaging CRO and the sites (Queries, Data Clarification Forms, test data submitted by the sites, etc.)
  - Native MRI data
  - Data processed and generated by the imaging CRO
  - Data generated by the reader (including image masks of liver and spleen and eCRFs)
  - Audit trails

**13.4.8 Unevaluable MRI:**

Unevaluable MRI data can result from a poor quality image, due to subject motion, improper organ coverage, technical problems with the image transmission to the imaging CRO, etc. The imaging CRO procedures for ensuring quality images are meant to reduce or eliminate such poor quality images.

If an adequate subject image cannot be obtained for a given time point in the study, the problem with the image will be documented at the imaging CRO and in the e\*CRF™. In addition, the imaging CRO will document all attempted corrective actions with the investigative site imaging centre.

**13.5 Appendix 5: WHO Common Toxicity Criteria**

| Category    | Toxicity                         | Grade0 | Grade1          | Grade2                                        | Grade3                                        | Grade4                                        |
|-------------|----------------------------------|--------|-----------------|-----------------------------------------------|-----------------------------------------------|-----------------------------------------------|
| Haematology | WBC (x103/l)                     | 4      | 3.0 - 3.9       | 2.0 - 2.9                                     | 1.0 - 1.9                                     | < 1.0                                         |
| Haematology | Platelets (x103/l)               | WNL    | 75.0 - normal   | 50.0 - 74.9                                   | 25.0 - 49.9                                   | < 25.0                                        |
| Haematology | Haemoglobin (g/dl)               | WNL    | 10.0 - normal   | 8.0 - 9.9                                     | 6.5 - 7.9                                     | < 6.5                                         |
| Haematology | Granulocytes/
Bands (x103/l)  | 2      | 1.5 - 1.9       | 1.0 - 1.4                                     | 0.5 - 0.9                                     | < 0.5                                         |
| Haematology | Lymphocytes
(x103/l)          | 2      | 1.5 - 1.9       | 1.0 - 1.4                                     | 0.5 - 0.9                                     | < 0.5                                         |
| Haematology | Haemorrhage                      | none   | mild, no        | gross, 1 - 2 units
transfusion per episode | gross, 3 - 4 units
transfusion per episode | massive, > 4 units
transfusion per episode |
| Coagulation | Fibrinogen                       | WNL    | 0.99 - 0.75 x N | 0.74 - 0.50 x N                               | 0.49 - 0.25 x N                               | < 0.25 x N                                    |
| Coagulation | Prothrombin
time(Quick)       | WNL    | 1.01 - 1.25 x N | 1.26 - 1.50 x N                               | 1.51 - 2.00 x N                               | > 2.00 x N                                    |
| Coagulation | Partial thrombo-
plastin time | WNL    | 1.01 - 1.66 x N | 1.67 - 2.33 x N                               | 2.34 - 3.00 x N                               | > 3.00 x N                                    |
| Metabolic   | Hyperglycaemia
(mg/dl)        | < 116  | 116 - 160       | 161 - 250                                     | 251 - 500                                     | > 500 or ketoacidosis                         |
| Metabolic   | Hypoglycaemia
(mg/dl)         | > 64   | 55 - 64         | 40 - 54                                       | 30 - 39                                       | < 30                                          |
| Metabolic   | Amylase                          | WNL    | < 1.5 x N       | 1.5 - 2.0 x N                                 | 2.1 - 5.0 N                                   | > 5.0 x N                                     |
| Metabolic   | Hypercalcaemia
(mg/dl)        | < 10.6 | 10.6 - 11.5     | 11.6 - 12.5                                   | 12.6 - 13.4                                   | 13.5                                          |
| Metabolic   | Hypocalcaemia
(mg/dl)         | > 8.4  | 8.4 - 7.8       | 7.7 - 7.0                                     | 6.9 - 6.1                                     | 6                                             |
| Metabolic   | Hypomagnesaemia
(mg/dl)       | > 1.4  | 1.4 - 1.2       | 1.1 - 0.9                                     | 0.8 - 0.6                                     | 0.5                                           |

| Category         | Toxicity                       | Grade0                  | Grade1                                      | Grade2                                                                    | Grade3                                                              | Grade4                                                                                    |
|------------------|--------------------------------|-------------------------|---------------------------------------------|---------------------------------------------------------------------------|---------------------------------------------------------------------|-------------------------------------------------------------------------------------------|
| Gastrointestinal | Nausea                         | none                    | able to eat reasonable intake               | intake significantly decreased but can eat                                | no significant intake                                               | —                                                                                         |
| Gastrointestinal | Vomiting                       | none                    | 1 episode in 24 hrs                         | 2 - 5 episodes in 24 hrs                                                  | 6 - 10 episodes in 24 hrs                                           | > 10 episodes in 24 hrs or requiring parenteral support                                   |
| Gastrointestinal | Diarrhoea                      | none                    | increase of 2 - 3 stools / day over pre-Rx  | increase of 4 - 6 stools / day, or nocturnal stools, or moderate cramping | increase of 7 - 9 stools / day, or incontinence, or severe cramping | increase of > 10 stools / day or grossly bloody diarrhoea, or need for parenteral support |
| Gastrointestinal | Stomatitis                     | none                    | painless ulcers, erythema, or mild soreness | painful erythema, oedema, or ulcers but can eat solids                    | painful erythema, oedema, or ulcers and cannot eat solids           | requires parenteral or enteral support for alimentation                                   |
| Liver            | Bilirubin (N = 17 $\mu$ mol/L) | WNL                     | -----                                       | < 1.5 x N                                                                 | 1.5 - 3.0 x N                                                       | > 3.0 x N                                                                                 |
| Liver            | Transaminase (SGOT, SGPT)      | WNL                     | 2.5 x N                                     | 2.6 - 5.0 x N                                                             | 5.1 - 20.0 x N                                                      | > 20.0 x N                                                                                |
| Liver            | Alk Phos or 5 nucleotidase     | WNL                     | < 2.5 x N                                   | 2.6 - 5.0 x N                                                             | 5.1 - 20.0 x N                                                      | > 20.0 x N                                                                                |
| Liver            | Liver- clinical                | No change from baseline | -----                                       | -----                                                                     | precoma                                                             | hepatic coma                                                                              |
| Kidney, bladder  | Creatinine                     | WNL                     | < 1.5 x N                                   | 1.5 - 3.0 x N                                                             | 3.1 - 6.0 x N                                                       | > 6.0 x N                                                                                 |
| Kidney, bladder  | Proteinuria                    | No change               | 1 (+) or < 0.3 g% or 3 g/L                  | 2 - 3 (+) or 0.3 - 1.0 g% or 3 - 10 g/L                                   | 4 (+) or > 1.0 g% or > 10g/L                                        | nephrotic syndrome                                                                        |
| Kidney, bladder  | Haematuria                     | Negative                | microscopic only                            | gross, no clots no Rx needed                                              | gross and clots bladder irrigation                                  | requires transfusion or cystectomy                                                        |
| Kidney, bladder  | Weight gain/ loss              | < 5.0 %                 | 5.0 - 9.9 %                                 | 10.0 - 19.9 %                                                             | 20.00%                                                              | -----                                                                                     |
| Pulmonary        | Pulmonary                      | none or no change       | asymptomatic, with abnormality in PFTs      | dyspnoea on significant exertion                                          | dyspnoea at normal level of activity                                | dyspnoea at rest                                                                          |

| Category   | Toxicity             | Grade0            | Grade1                                                                                                                    | Grade2                                                                                                                    | Grade3                                                                               | Grade4                                                                          |
|------------|----------------------|-------------------|---------------------------------------------------------------------------------------------------------------------------|---------------------------------------------------------------------------------------------------------------------------|--------------------------------------------------------------------------------------|---------------------------------------------------------------------------------|
| Cardiac    | Cardiac arrhythmias  | none              | asymptomatic, transient, requiring no therapy                                                                             | recurrent or persistent, no therapy required                                                                              | requires treatment                                                                   | requires monitoring; or hypotension, or ventricular tachycardia or fibrillation |
| Cardiac    | Cardiac function     | none              | asymptomatic, decline of resting ejection fraction by less than 20 % of baseline value                                    | asymptomatic, decline of resting ejection fraction by more than 20 % of baseline value                                    | mild CHF, responsive to therapy                                                      | severe or refractory CHF                                                        |
| Cardiac    | Cardiac ischaemia    | none              | non-specific T- wave flattening                                                                                           | asymptomatic, ST and T wave changes suggesting ischaemia                                                                  | angina without evidence of infraction                                                | acute myocardial infarction                                                     |
| Cardiac    | Cardiac- pericardial | none              | asymptomatic effusion, no intervention required                                                                           | pericarditis (rub, chest pain, ECG changes)                                                                               | symptomatic effusion; drainage required                                              | tamponade; drainage urgently required                                           |
| Cardiac    | Hypertension         | none or no change | asymptomatic, transient increase by greater than 20 mm Hg (D) or to > 150 / 100 if previously WNL. No treatment required. | recurrent or persistent increase by greater than 20 mm HG (D) or to > 150 / 100 if previously WNL. No treatment required. | requires therapy                                                                     | hypertensive crisis                                                             |
| Cardiac    | Hypotension          | none or no change | changes requiring no therapy (including transient orthostatic hypotension)                                                | requires fluid replacement or other therapy but not hospitalisation                                                       | requires therapy and hospitalisation; resolves within 48 hours of stopping the agent | requires therapy and hospitalisation for > 48 hrs after stopping the agent      |
| Neurologic | Neuro: sensory       | none or no change | mild paraesthesias; loss of deep tendon reflexes                                                                          | mild or moderate objective sensory loss moderate paraesthesias                                                            | severe objective sensory loss or paraesthesias that interfere with function          | -----                                                                           |
| Neurologic | Neuro: motor         | none or no change | subjective weakness; no objective findings                                                                                | mild objective weakness without significant impairment of function                                                        | objective weakness with impairment of function                                       | paralysis                                                                       |

| Category   | Toxicity            | Grade0            | Grade1                                                                 | Grade2                                                                                       | Grade3                                                                                          | Grade4                                          |
|------------|---------------------|-------------------|------------------------------------------------------------------------|----------------------------------------------------------------------------------------------|-------------------------------------------------------------------------------------------------|-------------------------------------------------|
| Neurologic | Neuro: cortical     | none              | mild somnolence or agitation                                           | moderate somnolence or agitation                                                             | severe somnolence, (>50 % waking hours), agitation, confusion, disorientation or hallucinations | coma, seizures, toxic psychosis                 |
| Neurologic | Neuro: cerebellar   | none              | slight incoordination, dysdiadochokinesia                              | intention tremor, dysmetria, slurred speech, nystagmus                                       | locomotor ataxia                                                                                | cerebellar necrosis                             |
| Neurologic | Neuro: mood         | no change         | mild anxiety or depression                                             | moderate anxiety or depression                                                               | severe anxiety or depression                                                                    | suicidal ideation                               |
| Neurologic | Neuro: headache     | none              | mild                                                                   | moderate or severe but transient                                                             | unrelenting and severe                                                                          | -----                                           |
